### **4.3 Statistical analysis**

Intervention effects on primary and secondary outcomes at 3 months after the intervention will be assessed based on repeated-measures linear mixed-effects multilevel models, which will include random cluster (site) effects [33]. Individual measures of change will therefore be modelled as the function of randomly assigned group, site, assessment time, and their interaction terms. Model-based estimations will be performed with an intention-to-treat approach (primary analyses) using the restricted maximum-likelihood method; the model assuming that missing values are missing-at-random. Analyses and estimations will also be performed with a per-protocol approach and an attrition propensity will be calculated using a logistic model predicting attrition with baseline values of site, allocation group, age, sex and body mass index. All the analysis will be conducted in men and women separately.

It should also be noted that the intervention effect assessments will not only be based on statistical and practical significance (as usually done), but also on a practical benefit approach emphasizing and reporting unadjusted values that are intuitive to human judgment and readily replicable considering the design and methodology of this project.

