#### **Ectopic fat depots**

Abdominal subcutaneous and intermuscular adipose tissue, as well as hepatic fat fraction will be quantified by magnetic resonance imaging (Siemens 3T Magnetom Vida). Semiautomatic software for tissue segmentation will be used to calculate visceral, subcutaneous, and intermuscular abdominal adipose tissue variables in all 3D abdominal volume: volume, cross-sectional area at selected levels, and mean/median fat fraction. These image markers will be derived from a standard 6 echo Dixon series. At L3 and L5 levels, we will obtain these image markers: cross-sectional area, muscular tissue, and intramuscular fat fraction. We will also quantify with a 6 echoes Dixon series, the fat fraction in all lumbar vertebral bodies, from a mid-sagittal image.

The segmentation of these areas will be manually edited. Lastly, we will measure image markers from mid-thigh. Again, using a 6 echoes Dixon series, we will obtain cross-sectional area, muscular tissue, intermuscular adipose tissue, fat fraction, subcutaneous adipose tissue, and bone marrow fat fraction. The segmentation for all these structures will be done with a semiautomatic proprietary algorithm.

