## **4.2 Sample size**

A recent systematic review and meta-analysis indicate that a VAT reduction of 6.1% is considered a clinically meaningful change even in the absence of weight loss [27]; previous exercise and nutrition intervention trials also showing changes in VAT ranging from 10 to 28% [28, 29]. The sample size calculations for VAT assume the study will be able to detect a mean difference of 10% in each intervention group from baseline to intervention endpoint, relative to the UC group. Therefore, assuming a standard deviation of 7% in VAT [28], the enrolment of 21 participants per arm will provide a statistical power of 90% at an alpha level of 0.008 (controlling for multiple group comparisons) to detect a minimum effect size of 10% in VAT. Considering subgroup analyses by sex and a maximum dropout rate of ~20%, we will recruit ~52 participants for each trial group; the total sample size being of ~208 participants (~104 in each study site).

To ensure a balanced sex distribution and maintain sufficient sample numbers despite projected dropouts, several strategies will be implemented:

- Recruitment process: We will employ a specific recruitment process that aims to enroll an equal number of men and women. For every woman recruited, we will request them to invite one man to participate in the study. This approach has proven successful in our previous intervention studies and has helped maintaining a balanced sex distribution [30-32].
- Sample size calculations: Our sample size calculations have taken into account subgroup analyses by sex. We have conservatively estimated a maximum dropout rate of approximately 20%. By considering this dropout rate, we have ensured that our study is adequately powered to detect the specified effect size even if there are differential dropout rates between men and women. For example, if men have a dropout rate of 5% and women have a dropout rate of

15%, our study will still have sufficient power to analyze the data separately in men and women.

- Expected dropout rate: While we have conservatively estimated the maximum dropout rate, we anticipate that the actual dropout rate will be relatively lower and similar between both sexes. This expectation is based on our previous studies and the measures we have in place to promote participant engagement and adherence [30-32].

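### The trial is powered on percent change in VAT, but section 4.3 fixes neither a percent or log scale nor a baseline-adjusted model; both should be specified.

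*Combined protocol and SAP*

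**What the plan says.** Section 4.2 (Sample size) works in percent. The study is assumed to be "able to detect a mean difference of 10% in each intervention group from baseline to intervention endpoint, relative to the UC group", with an SD of 7%, 90% power and an alpha of 0.008, which leads to "the enrolment of 21 participants per arm". Allowing for analyses by sex and about 20% dropout, this becomes about 52 per group.

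Section 4.3 (Statistical analysis) specifies repeated-measures linear mixed models with random site effects, applied to primary and secondary outcomes alike: "Individual measures of change will therefore be modelled as the function of randomly assigned group, site, assessment time, and their interaction terms". It does not say whether change is absolute, percent or logarithmic. Baseline covariates are listed only for the attrition model, and VAT is not among them. The section ends by describing a practical-benefit approach, "emphasizing and reporting unadjusted values that are intuitive to human judgment and readily replicable".

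Section 3.6 says that VAT is quantified by MRI. Section 3.7 (Ectopic fat depots) lists what is extracted from the abdominal volume: "volume, cross-sectional area at selected levels, and mean/median fat fraction". Neither section names one of these as the primary variable. Section 3.5 and the outcomes table give two assessments, baseline and 12 weeks.

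**The concern.** Two choices that determine the primary estimate are left open.

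The first is scale. A linear model on VAT as measured estimates a mean difference in absolute units. That cannot be set directly against the 10% design effect or the 6.1% threshold cited in section 4.2. If treatment acts proportionally, people with more VAT also lose more in absolute terms, so raw changes are more variable, and more so in a treated arm than in usual care. The power calculation then does not carry over.

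The second is the use of baseline. With free baseline means in each arm and two time points, the group-by-time term reproduces a comparison of change scores. This gives up precision that a baseline-adjusted analysis would recover from data already collected, and section 4.3 applies the same model to every secondary outcome.

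With several VAT measures and more than one possible scale, the plan also leaves room to choose the primary result after the data are seen.

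**Working it through.** **Inputs from the documents.** Difference 10%, SD 7%, alpha 0.008, power 90%, 21 per arm (section 4.2); two time points (section 3.5); model terms group, site, time and interactions (section 4.3).

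**Assumptions.** The 7% is read as the SD of percent change. Tests are two-sided. The between-person coefficient of variation (CV) of baseline VAT is not in the documents, so 30% to 60% is tried. Correlations for secondary outcomes are also not given.

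**1. The plan's own figure.** The normal-approximation formula is n = 2(z₁ + z₂)²(SD/difference)². With z₁ = 2.652 (two-sided 0.008) and z₂ = 1.282 (90% power), n = 2 × (3.934)² × 0.49 = 15.2, so 16 per arm. The t-based calculation gives 18. The stated 21 is not reproduced but errs on the safe side: t-based power at 21 is 96.2%. The step to 52 is consistent: 2 × 21 / 0.8 = 52.5.

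**2. What raw units do to the variance.** Write raw change as baseline × proportional change, with mean baseline m, coefficient of variation c, SD of percent change s = 7 and mean loss e. The variance of raw change, in units of (m/100)², is s²(1 + c²) + c²e². Take e = 0 in usual care and e = 10 in a treated arm.

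| CV | Usual care | Treated | Ratio |
|---|---|---|---|
| 30% | 49 × 1.09 = 53.4 | 53.4 + 9 = 62.4 | 1.17 |
| 40% | 49 × 1.16 = 56.8 | 56.8 + 16 = 72.8 | 1.28 |
| 50% | 49 × 1.25 = 61.3 | 61.3 + 25 = 86.3 | 1.41 |
| 60% | 49 × 1.36 = 66.6 | 66.6 + 36 = 102.6 | 1.54 |

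On the percent scale the variance is 49 in both arms.

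**3. Power on each scale.** Raw changes are skewed, so power was simulated: lognormal baseline, follow-up = baseline × (1 − effect + Normal(0, 0.07)), 21 per arm, 10% effect, two-sided alpha 0.008, 20,000 trials per setting.

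| CV | Raw change | Log change |
|---|---|---|
| 30% | 93% | 96% |
| 40% | 90% | 96% |
| 50% | 87% | 96% |
| 60% | 82% | 96% |

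The raw scale costs about 3 to 14 points. Measured against the 90% that section 4.2 claims, there is no shortfall at 30%, power sits on the line at 40%, and it is below at 50% and 60%.

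**4. Gain from baseline adjustment.** With equal variance σ² at both times and correlation ρ, a change score has variance 2σ²(1 − ρ), and a baseline-adjusted outcome has σ²(1 − ρ²). The ratio is (1 + ρ)/2:

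- ρ = 0.7: 0.85, so 15% less variance.
- ρ = 0.5: 0.75, so 25% less variance.

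For VAT, a 7% SD of change implies a log-scale correlation of ρ = 1 − 0.07²/(2 × ln(1 + c²)). This gives 0.972 at c = 0.3 and 0.992 at c = 0.6, hence ratios of 0.986 and 0.996, so at most about 1.4% less variance over this range. In simulations of 4,000 trials at CV 30% to 50%, log ANCOVA had 95% to 96% power and log change 96% to 97%, so there was no gain for VAT under this model.

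**The case against.** The strongest reply is that section 4.3 is silent on scale rather than wrong. Its wording about measures of change fits percent or log change as well as raw change. A reader might infer that the plan mandates raw VAT, and hence that it analyses a different quantity from the one it powered. The text does not say that; the mismatch is conditional on raw units being used.

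A reader might also infer that baseline is ignored. It is not. In a repeated-measures model with assessment time, baseline enters as a response, and the group-by-time contrast is unbiased under randomisation. Omitting a baseline covariate is an efficiency choice, not an error.

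On size, the surplus in 21 per arm absorbs the raw-scale loss up to a CV of about 40%, and no CV is given in the documents. The emphasis on unadjusted values is introduced as an addition to statistical assessment, so it does not define the primary model. Analysing percent change would match section 4.2 as well as log VAT does.

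All of this stands, and it limits the claim. Two things remain. The scale and the primary VAT measure are unspecified for an outcome powered in percent. And the model as written has neither a baseline covariate nor a common-baseline constraint, although either costs nothing and improves precision where correlation is moderate.

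**Conclusion.** The point holds as a specification gap with a conditional cost. Section 4.2 is in percent, section 4.3 fixes no scale, and its model reduces to a change-score comparison. That reduction takes participants measured at both times and assumes that a within-person covariance is fitted, which the repeated-measures label implies but the section does not spell out.

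- **Scale.** If raw VAT is used, the estimand departs from the powered one, and the power loss in step 3 applies. It assumes a proportional effect, a lognormal baseline and the CV range tried.
- **Baseline.** The loss of efficiency matters mainly for secondary outcomes with moderate correlation. The correlations of 0.5 to 0.7 are illustrative, and the formula assumes similar variance at both times. For VAT itself the gain is negligible.

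The documents do not support saying that the trial is underpowered for its 10% design effect, or that its planned comparison is biased. The change is worth making because it ties the primary estimate to the sample-size basis, removes a choice that could otherwise be made after seeing the data, and is nearly free.

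**What to change.** Amend section 4.3 before the analysis:

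1. Name one MRI VAT measure as primary (for example, volume over the full abdominal stack) and carry the same definition into section 3.6.
2. Analyse it on the log scale and back-transform the group contrast to a percent difference, so that it can be read against section 4.2.
3. For the primary and all continuous secondary outcomes, use a constrained longitudinal model (common baseline mean across arms, plus group by time) or ANCOVA of the 12-week value on the baseline value. State the within-person covariance.
4. Keep unadjusted means and changes as descriptive results only.

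The cost is SAP wording; no new data, visits or participants are needed. The small downside is that VAT effects are reported as percent differences, with absolute units given descriptively.

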## **5. ETHICAL ISSUES**

### **5.1 Institutional Ethics Committee Approval**

This study conforms to the last revised Ethical Principles for Medical Research Involving Human Subjects comprised in the Declaration of Helsinki. The experimental protocol was approved by the Servicio Andaluz de Salud (Comité Ético de Investigación Provincial de Granada) and the Comité Ético de Investigación Clínica de Navarra (PI\_2021/119).

## **5.2 Patient Consent**

All participants will receive accurate information on the study assessments and intervention, and written informed consent from each participant will be obtained prior to any data collection. Signed copies of the Consent Form and a Patient Information Sheet will be given to participants. Those participants unable or not willing to give informed consent will not be eligible for enrollment in this study.

The Patient Information Sheet will also clearly state that participants have the right to withdraw from the study at any time without prejudice or explanation.

## **5.3 Confidentiality and Privacy**

The confidentiality and privacy of all participants will be cautiously respected and ensured throughout the conduct of the study. All data will only be identified by a unique identification number/code given to each participant at the beginning of the trial; all data treatment and analyses being correspondingly blinded.

6. SUMMARY OF CHANGES TO STUDY PROTOCOL

| Date       | Amendment                                                                                                                                                                                                                                                                            |
|------------|--------------------------------------------------------------------------------------------------------------------------------------------------------------------------------------------------------------------------------------------------------------------------------------|
| 22/10/2021 | Institutional Ethics Committee approvals: Comité Ético de Investigación Clínica de Navarra (PI_2021/119). Section 3.1                                                                                                                                                                |
| 26/01/2022 | EXTREME: com.nnbi.app_extreme, NNBi2020 S L., Navarra, Spain                                                                                                                                                                                                                         |
| 2/02/2022  | Institutional Ethics Committee approvals: Servicio Andaluz de Salud (Comité Ético de Investigación Provincial de Granada). Section 3.1                                                                                                                                               |
| 05/04/2022 | First posted at ClinicalTrials.gov                                                                                                                                                                                                                                                   |
| 22/06/2023 | Development of an R script for analyzing continuous glucose monitoring R available at https://github.com/DIVA-soft/CGManalyzer . Section 3.7                                                                                  |
| 22/06/2023 | Development of an R script for analyzing data from accelerometers and continuous glucose monitors that have been time-aligned using the experimental tool available at https://github.com/DIVA-soft/GGIRmatcher . Section 3.7 |
| 22/06/2023 | Data analysis of accelerometer-derived outcomes using an R script with the version 2.10-3. Section 3.7                                                                                                                                                                               |
